#### Analysis of the secondary outcomes

The continuous secondary outcomes, to compare functional outcomes, disease-specific function, perceived level of pain, self-efficacy, fear avoidance, psychological distress and health-related quality of life between groups, are assessed through the corresponding PROMs measured at baseline, 6 months and 12 months post randomisation. Mixed effects models, as used in the primary analysis, will be used to assess these outcomes. These models will account for person within centre random effects, and Charlson Comorbidity Index score and the relevant baseline PROM score (as continuous outcomes), operation type, time (6 or 12 months) and treatment as fixed effects. Treatment by time point interactions will also be included in the model to allow time-specific treatment effects to be calculated.

There is expected to be a low number of complications/serious adverse events (SAEs) in this trial. Any adverse events (AEs) occurring whilst a participant is continuing in the study, until completion of the final study visit will be recorded. All AEs will be reported and tabulated by grade and treatment group—similar reporting will be done with SAEs. The number of SAEs and the number of participants reporting one or more SAEs will be reported by the treatment group. If there is a large enough number of events for a comparison to be appropriate, then the complications in each group will be pooled and the ‘Total Complications’ analysed by calculating the odds ratio and 95% confidence interval using logistic regression adjusting for minimisation factors (recruiting centre, Charlson Comorbidity Index (as a continuous value) and type of operation) and treatment.

#### Sensitivity analyses

Sensitivity analysis will assess the internal validity of the trial results by performing a per-protocol analysis on all participants who fall under the per-protocol definition as per the ‘Definition of analysis populations’ section.

##### Missing data

Missing data analysis will be performed on the primary outcome only. The primary analysis multi-level model using repeated measures is relatively robust to missing data under the missing at random (MAR) assumption [30].

Analysis will be performed on an intention-to-treat basis. The number and percentage of participants in the missing category will be presented, as well as reasons for missingness if known. Missing data will be reported and summarised by the treatment group. The distribution of missing data will be explored to assess the assumption of data being missing at random under which the principal analyses will be conducted. Varying scores of the UCLA Activity Score (e.g. 30th, 40th, 50th, 60th, 70th quantiles) will be imputed where data is missing and these ‘complete’ datasets will be reanalysed, using the same model used in the primary analysis and the results presented in graphical form. This analysis will be undertaken if there is more than 5% missing data for the primary outcome at 12 months.

If there is evidence that there is a departure from the MAR assumption, a search for factors not included in the primary analysis model that explains missingness will be performed and if variables are found, multiple-imputation using chained equations [31] will be utilised, using the primary analysis model but including these variables to assess the sensitivity of the findings to missing data. If no variables are identified, multiple-imputation will not be performed.

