## Methods

### Trial design

The trial is an open, phase III, pragmatic, parallel, two-arm, two-way superiority randomised controlled trial (RCT) on individuals investigating the effectiveness of usual care plus a group exercise and behaviour-change intervention versus usual care alone to increase physical activity following primary THR or TKR. Neither participants nor physiotherapists can be blinded to the treatment allocation. Primary comparison is assessed at 12 months post-randomisation with data being collected at baseline (pre-operatively), 6 months and 12 months post-randomisation.

Participants will be screened for inclusion in the trial pre-operatively, consented pre-operatively and eligibility confirmed post-operatively. They will then be randomised prior to hospital discharge and notified of their group allocation to facilitate the organisation of their rehabilitation. Initially, participants were randomised to the two groups 1:1 using minimisation by trial centre, type of joint replacement (THR or TKR), and Charlson co-morbidity index (1–3 or ≥4). The minimisation algorithm will have a probabilistic element of 0.8 included to ensure unpredictability of treatment assignment.

After 75 randomisations, the random allocation ratio was changed to 2:1 (Experimental Intervention: Usual Care). This change was made to ensure more participants were randomised to the experimental intervention group. The intervention is group-based and is designed to have three or more participants per group session. Based on evidence from early recruiting sites, there was difficulty to consistently fill sessions under a 1:1 allocation ratio. Therefore this change was deemed important to facilitate larger groups. This change was implemented by the Trial Management Group and approved by the Data Safety Monitoring Committee, Sponsor and Research Ethics Committee.

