
### Sample size

Two hundred fifty participants (125 per arm) are required to detect a standardised effect size of 0.4 with 80% power and 5% (2-sided) significance, allowing for 20% loss to follow-up. These calculations are based on the primary outcome at 12 months post-randomisation, assuming a baseline standard deviation of 2.5 [17] and a between-group difference of one. Our target standardised effect size is derived from the UCLA Activity Score’s minimal clinically important difference of 0.92 [17]. The sample size was increased to 260 to account for the change in allocation ratio, maintaining the same power and type I error rate.

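### The missing-data sensitivity analysis treats one imputed quantile as observed, which makes its intervals too narrow, and no planned analysis represents departures from MAR that differ between arms

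*SAP article*

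**What the plan says.** The Missing data section rests the primary repeated-measures model on MAR and adds two checks.

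- **Quantile grid.** "Varying scores of the UCLA Activity Score (e.g. 30th, 40th, 50th, 60th, 70th quantiles) will be imputed where data is missing". Each filled dataset is analysed with the primary model and the results are graphed. The trigger is more than 5% missing for the primary outcome at 12 months. The section does not say whether the quantile comes from the pooled scores or from each arm, whether the arms may take different quantiles, or how the variance is corrected for imputation.
- **Multiple imputation.** This step is conditional: "If there is evidence that there is a departure from the MAR assumption", variables outside the primary model that explain missingness are sought and used in chained-equations imputation. Otherwise: "If no variables are identified, multiple-imputation will not be performed".

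Elsewhere, Sample size plans for dropout, "allowing for 20% loss to follow-up". Trial design describes an open trial, and the COVID-19 section says that all outcomes are patient-reported.

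**The concern.** A missing-data sensitivity analysis should show how far the primary result depends on MAR, with honest uncertainty. In an open trial with a self-reported outcome, a credible threat is that participants lost from one arm differ in activity from those who stay, in a way that the other arm does not mirror. A method that moves the missing values in both arms together may produce a flat graph in that situation, and a flat graph is normally read as robustness. Filling gaps with a fixed value and analysing it as data also narrows the intervals without adding information.

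**Working it through.** **The plan's own figure.** Sample size uses a difference of 1, SD 2.5, 80% power and two-sided 5%. n per arm = 2 × (1.96 + 0.84)² / 0.4² = 98.1, so 99, and 198 / 0.8 = 248. The t-test version needs 100 per arm, and 200 / 0.8 = 250, as stated. The planning inputs are therefore used below.

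**Inputs.** d = 1, SD 2.5, and missing fraction m = 20% per arm (the planned allowance; the actual 12-month rate is not given). Arm sizes follow from 230 randomised and the allocation change, "After 75 randomisations, the random allocation ratio was changed to 2:1 (Experimental Intervention: Usual Care": usual care 37.5 + 155/3 = 89 and intervention 141, approximately. Assumptions not in the SAP article: control mean 5, correlation 0.5 between time points, no centre effect, only 12-month scores missing.

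**1. Point estimate.** Let mE and mC be the missing fractions and q a value common to both arms.
Estimate = (1-mE)(5+d) + mE·q - (1-mC)·5 - mC·q.
- Equal fractions: q cancels and the estimate is (1-m)d = 0.80 at every quantile (simulated mixed model: 0.79 to 0.83).
- 25% intervention, 15% control: 0.25 + 0.10q, giving 0.68, 0.74, 0.81, 0.87, 0.94 from the 30th to the 70th quantile.
- 30% and 10%: -0.30 + 0.20q, giving 0.54 to 1.08.
- Quantiles taken within arm, same quantile in both: (1-m)d + m(qE - qC). With equal SDs qE - qC = d, so the estimate is d = 1 and the shrinkage disappears.

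**2. Standard error.** In a two-sample comparison, filling at the mean leaves variance (1-m)SD² on n values, against SD² on (1-m)n observed values. The SE ratio is √(1-m) / √(1/(1-m)) = 1-m, that is 10%, 20% and 30% too small for m = 0.1, 0.2 and 0.3. Away from the mean the loss is a little less (about 17 to 20% over the grid at m = 0.2). In a simulated random-intercept model with baseline, time, treatment and their interaction (100 runs), SE fell from 0.323 to between 0.281 and 0.286: 1 - 0.286/0.323 = 11% and 1 - 0.281/0.323 = 13%.

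**3. What this does to coverage.**
- *Pooled quantile:* simulated coverage was 89 to 90%, against 96% for available data (Monte Carlo error 2 to 3 points). This is what the shrinkage alone predicts: (1 - 0.806)/0.281 = 0.69, and Φ(1.96 - 0.69) - Φ(-1.96 - 0.69) = 0.898 - 0.004 = 89%.
- *Within-arm fill near the mean:* the estimate is in effect the observed difference, with its full sampling error, but is given an SE 0.8 times as large. Coverage in a two-sample comparison is 2Φ(1.96 × 0.8) - 1 = 88%.

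**4. Departure confined to one arm.** Suppose the 20% missing in the intervention arm are truly 2 points lower and those missing in usual care are not. The true difference is 1 - 0.2 × 2 = 0.6.

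| Analysis | Result |
|---|---|
| Truth | 0.6 |
| Available-data mixed model | 0.96 |
| Pooled quantile, mixed model (30th, 50th, 70th) | 0.78, 0.78, 0.79 |
| Pooled quantile, closed form | 0.80 throughout |
| Within-arm, same quantile (closed form 1.0) | 0.98 to 0.99 simulated |

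The grid is flat on either reading. The pooled version lies nearer the truth only because it shrinks every result towards zero.

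**The case against.** Four points can fairly be made for the plan.

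- **The text does not say that both arms receive one constant.** This stands. Within-arm quantiles would remove the shrinkage, and crossing quantiles between arms would restore sensitivity: 30th against 70th moves the difference by 0.2 × 2 × 0.524 × 2.5 = 0.52. But nothing in the section provides for crossing, and within-arm use of the same quantile still gives a flat grid with intervals that are too narrow.
- **The grid is a crude MNAR-type analysis.** A reader might infer that it cannot reveal MNAR bias at all. The documents do not support that: it moves when missing rates differ (0.68 to 0.94 at 25% and 15%), and missingness is to be summarised by arm.
- **The chained-equations step has a proper use.** MAR is conditional on the variables in the model. Observed data can show dependence on measured variables outside it, and imputation that includes them is legitimate if MAR then holds. What observed data cannot establish is MNAR, and this step does not address it.
- **The grid runs on its own trigger.** It would be wrong to say that nothing is done when no predictors are found; only multiple imputation is dropped.

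A reader might also expect the smaller SE to create false significance. On the pooled reading it does not: estimate and SE shrink together (1.018/0.323 = 3.15 for available data, 0.806/0.281 = 2.87 after filling). On the within-arm reading the ratio is inflated, by about 1/0.8 = 1.25 in a two-sample comparison.

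**Conclusion.** The point holds in limited form. Each grid result comes from a single fixed imputation treated as data, and its interval is narrower than the observed data justify, by about 11 to 13% in the simulated mixed model and up to about 20% in a two-sample comparison. With a pooled quantile the difference is also multiplied by about 0.8. With similar missing rates and the same quantile in both arms, the grid stays flat under an arm-specific departure that changes the true difference from 1 to 0.6. The conditional multiple imputation does not fill that gap, so no planned analysis represents arm-specific MNAR.

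These sizes rest on an assumed 20% missing in each arm, SD 2.5 and the simulation settings above; the SE effect scales with the missing fraction. This is a weakness in a sensitivity analysis. It does not alter the primary estimate, interval or test.

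**What to change.** Keep the 5% trigger and make the analysis independent of any check on MAR. Replace the quantile grid with:

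1. Multiple imputation of missing UCLA scores by arm, using the primary-model covariates, baseline and 6-month UCLA, and any predictors of missingness found.
2. Delta shifts added to the imputed 12-month values, varied separately in each arm (one arm at a time and both together) over a range fixed in advance and justified clinically.
3. The primary model fitted to each imputed dataset, combined by Rubin's rules, and displayed as a tipping-point plot over the two deltas.

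Zero shift in both arms gives the MAR result as a reference point and absorbs the present chained-equations step. The cost is revised SAP wording, modest extra programming and a judgement about the delta range. Trial status describes follow-up as ongoing with data lock still to come, so on that timetable the change can be made before the data are seen.

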#### Analysis of the primary outcome

The primary outcome measure, the role of usual care versus usual care plus the experimental intervention upon the UCLA Activity Score at 12 months post-randomisation, will be modelled using a mixed effects model. This model will account for person within centre random effects, and Charlson Comorbidity Index score and baseline UCLA Activity Score (as continuous outcomes), type of operation the patient is undergoing (THR or TKR), time (6 or 12 months) and treatment as fixed effects. Treatment by time point interactions will also be included in the model to allow time-specific treatment effects to be calculated. This model uses all available data at each time point. Comparison will be performed on an intention-to-treat basis and results presented as comparative summary statistics (i.e. difference in means) with 95% confidence intervals.

The appropriateness of the assumption of approximate normality of the residuals of this model will be assessed graphically. If the residuals are not normally distributed, the outcome data will be log-transformed to gain normality and geometric means with 95% confidence intervals will be reported. If data is not normally distributed after log-transformation, the non-parametric Mann-Whitney test will be used with no adjustment for baseline or stratification factors, and the difference in medians with 95% confidence intervals will be reported.

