#### Additional analysis

A mediation analysis will be carried out. A priori mediation analysis mediators will include self-efficacy, fear avoidance, pain and psychological distress to compare the mediation pathways presented in the BeST intervention [33] to the PEP-TALK intervention.

An additional analysis will be performed to assess the effect of COVID-19 on the activity at 12 months post-randomisation. The model used for the primary analysis will be extended to include COVID-19 status (as a fixed effect) and a COVID-19 status by time point interaction. The adjusted mean difference of COVID-19 status will be reported with supporting 95% confidence intervals. It should be noted that formally investigating COVID-19 status’ effect on activity is outside the scope of the original trial design so results from this analysis are hypothesis-generating and exploratory.

Descriptive statistics on secondary outcomes of GSES, the Tampa Scale for Kinesiophobia, HADS, EQ-5D-5L Index, EQ-VAS and NRS for pain may be produced to further assess the impact of COVID-19. No formal analysis to examine the relationship between COVID-19 status and secondary outcomes will be performed.

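### As worded, the multiple-imputation check could put post-randomisation variables into the treatment-effect model, so a changed estimand could be mistaken for sensitivity to missing data

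*SAP article*

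**What the plan says.** The Missing data section describes two checks on the primary outcome.

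- **Quantile imputation.** Fixed quantiles of the UCLA score replace the missing values, and the completed datasets are "reanalysed, using the same model used in the primary analysis and the results presented in graphical form".
- **Multiple imputation.** If there is evidence of a departure from missing at random, "a search for factors not included in the primary analysis model that explains missingness will be performed". Then, "if variables are found, multiple-imputation using chained equations [31] will be utilised", and the sentence continues "using the primary analysis model but including these variables to assess the sensitivity of the findings to missing data". If no such variables turn up, there is no multiple imputation.

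The primary model (Analysis of the primary outcome) has random effects for person within centre. It adjusts for Charlson score, baseline UCLA score, "type of operation the patient is undergoing (THR or TKR), time (6 or 12 months) and treatment as fixed effects", plus the treatment-by-time interaction. Apart from visit time, none of these covariates arises after randomisation.

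Under Additional analysis the plan states: "A priori mediation analysis mediators will include self-efficacy, fear avoidance, pain and psychological distress". According to Analysis of the secondary outcomes, these constructs are "assessed through the corresponding PROMs measured at baseline, 6 months and 12 months post randomisation".

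**The concern.** Two features of the multiple-imputation sentence combine badly. First, what it modifies is the primary analysis model, which produces the treatment effect. Secondly, the search admits any variable outside that model, whenever it was measured.

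The 6-month scores for self-efficacy, fear avoidance, pain and distress lie outside the primary model and precede the 12-month questionnaire, so they qualify for the search. So does attendance. If treatment affects such a variable and the variable affects activity, conditioning on it removes the part of the effect that runs through it. The coefficient is then no longer the total intention-to-treat effect.

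What is at stake is how the check is read. It exists to show whether missing data matter. If the estimand changes together with the handling of missing data, a smaller estimate cannot be attributed to either one, and could be reported as fragility to missing data even where the imputation worked well.

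**Working it through.** **1. What the sentence modifies.** Elsewhere the plan uses similar phrasing for changes to the fitted outcome model:
- Supporting analyses: the area-under-the-curve analysis takes the primary mixed model with a stated change to the time effect.
- Pre-specified subgroup analysis: the primary model is extended by an interaction.
- Additional analysis: the primary model is extended by COVID-19 status.

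The quantile check, by contrast, keeps the primary model as it is. Side by side, the plain reading is that the variables found are added to the treatment-effect model.

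**2. Planning figures, used only to set the scale.** The Sample size section assumes a difference of 1 and an SD of 2.5, to "detect a standardised effect size of 0.4 with 80% power and 5% (2-sided) significance, allowing for 20% loss to follow-up".
- Normal approximation: 2 × (1.960 + 0.842)² / 0.4² gives 99 per arm after rounding up. 99/0.8 gives 124 per arm, 248 in total.
- t-test version: 100 per arm, and 200/0.8 = 250, the stated figure.
- With 75 allocated 1:1 and 185 allocated 2:1, the arms are 37.5 + 61.7 = 99.2 and 37.5 + 123.3 = 160.8. After 20% loss the power is 0.800, so 260 reproduces too.

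The point does not rest on these figures.

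**3. Algebra of the shift.** Let T be treatment, M a 6-month mediator and B a standardised baseline covariate. Let s be the share of the effect that runs through M.

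- M = aT + u, with a = 0.5
- Y = (1 − s)T + bM + 1.25B + e, with b = s/a

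The total effect is (1 − s) + ab = (1 − s) + s = 1. With M in the analysis model, the coefficient of T is 1 − s.

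**4. Simulation.** There were 230 participants (the number randomised), with probability 0.6 of the experimental arm, true total effect 1.0 and SD about 2.5. The probability of a missing 12-month score was 1/(1 + exp(1.55 + 0.7M)), which gives about 17% missing. Each scenario had 1,500 runs of 10 imputations, and the imputation model always contained T, B and M. Mean estimates:

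| Assumed share s | 1 − s | Full data | Complete cases, M not adjusted | Imputed, M auxiliary only | Imputed, M also in analysis model |
|---|---|---|---|---|---|
| 0 | 1.00 | 1.003 | 1.000 | 0.999 | 1.002 |
| 25% | 0.75 | 0.978 | 0.964 | 0.981 | 0.734 |
| 50% | 0.50 | 1.009 | 0.983 | 1.013 | 0.512 |
| 75% | 0.25 | 0.999 | 0.953 | 0.998 | 0.251 |

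The last two columns use the same imputed data. Their differences are −0.003, 0.247, 0.501 and 0.747, which match s. The auxiliary-only column stays within 0.004 of the full-data column, so the fall comes from adjusting for M and not from missing data.

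A second simulation (600 trials per scenario, 20 imputations, same total effect) took shares of 20%, 40% and 60%. It gave 1.01 to 1.03 with the variable as auxiliary only, and 0.83, 0.62 and 0.41 with it also in the analysis model.

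**The case against.** The strongest reply is that the sentence describes how the imputation is built: the primary model's variables plus the predictors of missingness. That would be sound practice. The paragraph's closing rule supports this reading, since dropping imputation when no extra variables are found makes sense if their job is to inform it. The wording of the quantile check is also weaker evidence than it looks, because fixed-value replacement has no imputation model to name. And the section states that analysis is by intention to treat, which does not suggest a deliberate move to a direct effect.

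This stands as far as it goes: the benign reading is possible. But on that reading the article names no analysis model for the imputed datasets, so a clarifying sentence is needed either way.

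Further limits also stand:

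- Harm needs a departure from missing at random, a search that finds something, a treatment-affected variable among the finds, and its placement in the outcome model. Baseline predictors are equally eligible and would not cause it.
- Nothing in the documents shows that post-randomisation variables are the likelier predictors. The 6-month scores may themselves be missing for people who leave early.
- The mediated shares, the missingness mechanism and the missing rate are assumed. The re-derived simulation in the table uses a single 12-month endpoint, not the two-visit mixed model.

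A reader might infer that the plan sets out to adjust for its mediators. It does not say so: the mediators are named for a separate analysis, and the missing-data wording merely fails to keep them out.

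**Conclusion.** The point holds in limited form. Followed as worded, the rule permits a treatment-affected variable in the outcome model, and the multiple-imputation check would then compare two different estimands. Under a simple linear mediation model the estimate becomes about one minus the mediated share of the total effect. That share is not given in the documents, so the figures above show a mechanism and a range; they do not predict this trial's result.

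Three stronger conclusions are tempting and unsupported:

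- **That the primary result is biased.** It is not touched. This is a conditional sensitivity analysis, and the quantile check keeps the primary model.
- **That the estimate would fall below the minimal important difference of 0.92.** With a true effect of 1.0, any share above 1 − 0.92 = 8% would do this, but both the true effect and the share are assumptions.
- **That the check can never answer its question.** With baseline predictors only, or with the variables confined to the imputation, it can.

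The change is worth making because the ambiguity is real, the consequence would be misread, and the remedy is nearly free.

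**What to change.** In the Missing data section, state that:

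1. variables found to explain missingness enter the imputation model only, as auxiliary variables, alongside the variables of the primary model;
2. each imputed dataset is analysed with the primary model exactly as given under Analysis of the primary outcome, and the estimates are pooled by Rubin's rules;
3. if any variable is nevertheless added to the analysis model, it must have been measured before randomisation.

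Imputing separately by arm is an optional refinement, and the fix does not depend on it. The cost is one or two sentences of wording, with no extra data and no material analysis time.
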